## Abstract

**Objectives:**

Teleworking from home was widespread during the 2019 coronavirus disease pandemic. This working practice is expected to maintain popularity among employers and employees. Compared with in-person workers, teleworkers tend to be less physically active and have more musculoskeletal pain. Interventions specific to reducing health risks among teleworkers have not been identified. This study will examine the effects of an occupational lifestyle intervention encompassing 3 components: physical activity promotion, musculoskeletal health, and work environment improvement.

**Methods:**

This cluster randomized trial will have a target sample size of 500 participants. The target population is healthy adults aged 18-64 years who telework at least once per week. Randomization will be conducted on a stratified block basis for clusters of 20 to 100 individuals within the recruited companies. The intervention period will be 12 weeks and comprise individual (online lectures, feedback, and periodic email messages), sociocultural (team building through step competition), physical (poster and tabletop pop-up), and organizational (encouraging message from an executive) strategies. The intervention group will be compared with a wait-list control group. The primary outcome will be the number of steps taken, as assessed by an accelerometer, and the secondary outcomes will be musculoskeletal pain and a telecommuting environment. The study protocol was registered with the University Hospital Medical Information Network Clinical Trials Registry (ID: UMIN000053861) (https://center6.umin.ac.jp/cgi-open-bin/ctr/ctr.cgi?function=brows&action=brows&recptno=R000061478&type=summary&language=J).

**Results:**

Study enrollment began in March 2024, and the intervention will be completed by March 2025.

**Conclusions:**

The results of this study are expected to provide helpful data for promoting healthy teleworking practices.

## 1. Introduction

Teleworking from home, which became widespread during the 2019 coronavirus disease pandemic, is expected to maintain popularity among employers and employees.^1^ Teleworking from home is defined as “work that takes place fully or partly within the worker’s own residence,”^2^ and has several advantages for workers, such as reduced commuting burdens and improved work-life balance.^3^ In 2019, Japan enacted a law to reform work styles and secure a diverse workforce to address a serious labor shortage.^4^ Telework is attracting attention in this context as a flexible work style. Hybrid models, such as 3 days of office work and 2 days of telework, have also been established,^5^ and the percentage of teleworking companies in Japan’s capital city of Tokyo has remained at over 40% even after the pandemic .^6^

Although teleworking from home brings about changes in workers’ daily lives, several health risks associated with these changes have been reported in recent years. The first is a decrease in physical activity (PA) due to the lack of commuting and office mobility. Teleworkers tend to be less physically active and spend more time sitting than their commuting counterparts do,^7^ a behavior that increases an individual’s risk for future lifestyle-related diseases^8^^,^^9^ and falls^10^ associated with reduced physical fitness. The second reason is the occurrence of physical symptoms associated with an inadequate work environment at home, such as eye strain and musculoskeletal pain.^11^ There is an urgent need to identify strategies to reduce these health risks and sustain teleworking with healthy lifestyles.

Interventions for these health risks can be synergistic by means of a comprehensive approach that simultaneously addresses PA, musculoskeletal health, and the work environment. Reducing sedentary behavior and increasing PA contribute to the improvement of physical symptoms such as low back pain (LBP).^12^ Considering that a poor telecommuting environment is closely associated with physical symptoms,^11^ improvement of the environment is expected to decrease physical symptoms. In participants who have physical symptoms, it is assumed that improvement in these symptoms will increase physical activity. In addition, this synergistic comprehensive approach will meet the diverse needs of workers and enhance the feasibility of interventions.

Considering that this is a workplace intervention, a multicomponent approach that addresses not only the individual level but also the environmental, organizational, and other levels is needed. Many workers are aware of the benefits of engaging in healthy behaviors, but implementation is hampered by factors such as a tightly controlled work environment and differences in perspective between employers and employees.^13^ For example, without a common understanding that staying active at work or viewing health videos is beneficial, colleagues may perceive these behaviors as counteractive to the employer’s mission. A multicomponent intervention was effective in promoting PA in the workplace based on the social-ecological model,^14^^,^^15^ a theory that indicates that human behavior is influenced not only by intraindividual characteristics but also by multilayered factors such as individuals, organizations, regions, and policies.^16^

To the best of our knowledge, there has been no approach that comprehensively addresses the health risks of teleworkers. In terms of individual approaches, previous studies that focused on PA^14^^,^^15^ considered not only the individual employee but also the office environment and the upper management of the organization. However, it is necessary to demonstrate the effectiveness of these approaches for teleworkers,^17^ who have a low frequency of office attendance and face-to-face communication with colleagues and supervisors. Previous studies assessing improvements to the physical environment have reported the effect on musculoskeletal health.^18^ This approach was in the office environment, whereas no studies have examined the approach in the telework environment. The only study that has conducted ergonomics training for teleworkers^19^ had a limited number of participants and study period. Therefore, a high-quality study focused on improving telecommuting environments is required.

### 1.1. Objectives

This study aims to examine the effects of an occupational lifestyle intervention encompassing 3 components—PA promotion, musculoskeletal health, and work environment improvement—among Japanese teleworkers. The 12-week intervention program comprises individual (online lectures, feedback, and periodic email messages), sociocultural (team building through step competition), physical (poster and tabletop pop-up), and organizational (encouraging message from an executive) strategies. The primary hypothesis of the study is that the intervention group will have a significantly greater change in step count over 12 weeks than the control group. The secondary outcomes will be changes in other PA parameters, physical symptoms such as LBP, and the telecommuting environment.

### 1.2. Trial design

The proposed study is a 2-arm cluster-randomized controlled trial (cRCT) with a wait-list control group. After enrollment, each cluster (workplace) will be assigned to the intervention or control group in a 1:1 ratio using stratified block randomization. The effectiveness of the intervention program will be assessed by evaluating data from the intervention and control groups for the first 12 weeks at the employee level. The control group will not be provided with any program elements during this period. However, they will be provided with the program after the waiting period, and data from this program period will be used, along with data from the intervention group, for explanatory analyses.

## 2. Methods

### 2.1. Participants

This study began in March 2024 in the Japanese workplace and will continue until March 2025. The eligibility criteria for employees are: (1) being aged ≥18 years and <65 years; and (2) being home-based teleworkers for at least 1 d/wk. The exclusion criteria for employees are: (1) being prohibited from exercising by their doctors; (2) planning long-term business trips or retirement during the study; (3) being pregnant or possibly pregnant; and (4) being judged by the research director to be inappropriate for inclusion, for example, not agreeing to return the measuring instruments. Recruitment will be conducted through the research team’s network of companies that employ teleworkers. The employee coordinator of the company that agrees to participate will send invitations to employees who meet the eligibility criteria. Based on the employees who agree to participate at this stage, clusters of 20 to 100 participants will be selected and allocated to units, such as departments and offices, where contamination does not occur. Subsequently, participants will receive baseline survey instructions and instruments.

### 2.2. Interventions

The 12-week multicomponent occupational lifestyle intervention will be provided using a remote system (Figure 1). The program focuses on 3 topics: improving PA, musculoskeletal health, and the work environment. The intervention program comprises individual, sociocultural environment, physical environment, and organizational strategies based on the social-ecological model.^14^^-^^16^ We plan to collaborate with an employee coordinator at each site to ensure the successful delivery and implementation of the intervention. Additionally, the intervention can be tailored to each workplace’s specific circumstances (eg, in cases where some programs cannot be introduced). The implementation of other health promotion programs by each company during the study period will be generally permitted.

**Figure 1 f1:**
[figure not shown]
Multicomponent occupational lifestyle intervention.

#### 2.2.1. Individual strategy

Individual strategies include online lectures, feedback, and email messages. First, we established a website where participants can access online lectures about improving PA, musculoskeletal health, and their work environment at their convenience from any location.

The PA section consists of 3 theoretical lectures (4-5 minutes each) and specific exercise movies (2-5.5 minutes each). The researcher ([name]) will deliver theoretical lectures on PA promotion. The content will include definitions of PA and sedentary behavior, the impact of physical inactivity and sedentary behavior on health, and evidence of “+10 minutes of PA per day.”^20^ The lectures on specific exercise methods contain five 3-minute stretching exercises (produced by Science Tokyo and Nomura Real Estate Group) focused on locomotion training for workers.^21^ In the musculoskeletal health section, we will provide 7 short videos of exercises (1.5-4 minutes each) and 5 videos of evidence-based information on LBP (2-4 minutes each). Exercise programs consist of muscle stretching and strengthening to improve postural alignment and spinal stability. The exercise menu comprises 7 therapeutic self-exercises, including standing back extension “One stretch,”^22^ trunk lateral flexion, sitting trunk extension, seated hamstring stretch, lying trunk twisting, lunge exercise, and arm-leg raising. Educational videos comprise 5 tips with information on LBP management (staying active, importance of self-management, fear-avoidance belief, psychological stress, and no need to be concerned about spine imaging findings). [name]’s research team created these educational videos with reference to several clinical guidelines and media campaigns for LBP.^23^ We will also provide pamphlets on LBP management, which include biomechanical (eg, posture, exercise) and psychosocial aspects (eg, psychological stress at the workplace and fear-avoidance beliefs).

In the work environment section, 5 videos were created by one researcher ([name]) on improving the telework environment at home (2-4 minutes each). The content of each video covers 9 themes and 12 environmental improvement actions, referring to previous studies,^11^ a technical brief,^24^ a checklist,^25^ and others. The content covers topics such as illumination and displays, keyboards and mice, feet and chairs, temperature, humidity, air quality, and noise. These videos include several behavioral science findings to inspire action. For example, quizzes will be administered. Information-gap theory, which states that people are intrigued by what they do not understand, has been referenced.^26^

As feedback, participants in the intervention group will receive an occupational health report about 3 topics. The PA report will include daily step counts; light, moderate, vigorous, and moderate-to-vigorous PA that has been undertaken; sedentary time; prolonged sedentary time; and recommended standards. All of these figures will be provided separately for teleworking days and office days. The musculoskeletal health report will include LBP pain intensity (based on a numerical rating scale, 0-10). The work environment report will include environmental sensor measurements (temperature, relative humidity, illuminance, and noise level) and their recommended ranges. Additionally, an evaluation of telework environment improvement actions will be presented. This evaluation will be based on telework environment improvement behavior in the outcomes of this study.^11^^,^^24^^,^^25^

The intervention group will be provided with email messages twice a week—on Tuesdays and Fridays—for 12 weeks. The content of the messages will include requests for active participation, recommendations based on baseline surveys, PA promotion, LBP prevention tips, and work environment improvement methods. The research team will send the messages to the intervention group’s coordinator, who will then email them to the participants. To improve adherence in companies with joint meetings, researchers will ask their supervisors to conduct the exercises that were most recently distributed via email in a group setting. The frequency of implementation will be measured in a post-survey. Employees who will not participate in the study may not be prohibited from receiving the intervention program in part.

#### 2.2.2. Sociocultural environment strategy

The intervention group will undertake a step competition to create an atmosphere that encourages participants to actively engage in the program. This competition will include individual and team components, with the results announced through weekly messages.

#### 2.2.3. Physical environment strategy

The intervention group will receive posters aimed at promoting PA. These posters will be accessible on a notice board in the office or on a website. The topics will include the health risks associated with prolonged sitting, health benefits of replacing sitting with standing, health benefits of walking, and importance of goal-setting for improving PA. Posters will be replaced with new posters every 3 weeks.

The pamphlet on LBP management mentioned above will include a tabletop pop-up that individuals can easily create. The tabletop pop-up will show how to do “One stretch,” with illustrated instructions. We will encourage the intervention group to create the tabletop pop-up to place on their work desk when we deliver the pamphlet.

#### 2.2.4. Organizational strategy

As an organizational strategy, encouraging messages from upper management will be provided to the participants in the intervention group. The content of the mailings will be determined by each upper management, but will include the importance of participation and specific encouragement based on baseline survey results.

### 2.3. Outcomes

#### 2.3.1. Physical activity

The primary outcome is the change in daily step count between baseline and the end of the intervention. The secondary outcomes include changes in light, moderate, vigorous, and moderate-to-vigorous PA; sedentary time; and prolonged sedentary time. Participants will be asked to wear a triaxial accelerometer (Active-style Pro HJA-350IT; Omron Healthcare, Kyoto, Japan) on their waist for 14 days.^27^^,^^28^ For safety reasons, participants will be requested to remove the device when sleeping, bathing, swimming, or playing contact sports. Additionally, participants will maintain a daily diary of whether they were working, their working time, and the type of work they were doing (remote or commuting). Finally, we will use valid accelerometer data (at least 10 h/d^29^ and a minimum of 3 valid days) in the analysis.

#### 2.3.2. Musculoskeletal health

The outcomes of the musculoskeletal health section will include the intensity of LBP (numerical rating scale, 0-10), degree of disability due to LBP, attitude/belief about LBP, work productivity, subjective improvement in LBP, and frequency of exercise performed (individual/group). Disability due to LBP will be indicated according to 4 grades: grade 0 (no LBP) to grade 3 (LBP interfering with work and leading to sick leave), with a modification of Von Korff’s grading method.^30^ Attitude/belief about LBP will be assessed using the 5 statements about fear-avoidance beliefs and passive coping strategies on a 4-point Likert scale (1 = strongly disagree, to 4 = strongly agree). Work productivity will be assessed using the presenteeism item in the LBP version of Work Productivity and Activity Impairment (WPAI),^31^ and subjective improvement in LBP will be assessed using the Patient’s Global Impression of Change (PGIC).^32^ Participants will be asked, “Since the start of the study, how has your LBP changed?” The options will be rated on a 7-point Likert scale (1 = very much improved, to 7 = very much worse).

#### 2.3.3. Work environment

The telecommuting environment will be assessed objectively and subjectively. The objective telework environment will be measured on the worker’s desk at 10-minute intervals using an environmental sensor (2JCIE-BL01; Omron, Kyoto, Japan). The measurement parameters will include temperature, relative humidity, illuminance, and noise level. For comparison purposes, measurements will be conducted at representative points in the office in the same manner. For the analysis, teleworking environment data during the working hours of each worker will be extracted based on a diary survey. Office environment data will be extracted from 9:00 am to 5:00 pm (excluding midday to 1:00 pm) on weekdays, considering regular work time.

Subjective telework and office environments will be assessed by workers using the Subjective Assessment of workplace Productivity (SAP) questionnaire.^33^ The workers’ satisfaction with the telework and office environments (including lighting, thermal, air, sound, spatial, and IT environment) will be assessed on a 5-point Likert scale (1 = dissatisfied, to 5 = satisfied). Additionally, whether the respondent has taken action to improve the telecommuting environment will also be evaluated. As there is no existing scale for this assessment item, a 12-behavior questionnaire was created based on previous research,^11^ a technical brief,^24^ a checklist,^25^ and others. Each item will be rated on a 5-point Likert scale (1 = not applicable, to 5 = applicable).

Improvements in these teleworking-environment behaviors are expected to improve somatic symptoms.^11^ Therefore, the Somatic Symptom Scale-8 (SSS-8)^34^ will be used to evaluate somatic symptoms for the secondary outcomes.

#### 2.3.4. Work-related and psychological outcomes

Work productivity and psychological status, estimated to be affected by improvements in PA and physical symptoms, will be assessed. Participants’ presenteeism will be assessed using the Japanese version of the World Health Organization Health and Work Performance Questionnaire (WHO-HPQ).^35^ Work engagement will be measured using the Japanese version of the Utrecht Work Engagement Scale (UWES-9), which evaluates 3 dimensions: vigor, dedication, and absorption.^36^ For psychological outcomes, mood and anxiety disorders will be measured using selected questions from the Japanese version of the Kessler Psychological Distress Scale (K6).^37^

#### 2.3.5. Process evaluation after the intervention

The degree of participation and satisfaction (eg, whether the participants consumed each piece of content, whether they took informed action, their impressions of the frequency of delivery and content, and whether there was an atmosphere of workplace-wide commitment and satisfaction) will be surveyed after the intervention. An interview will also be conducted with some of the study participants after the intervention to assess the feasibility and effectiveness of, and barriers to, the program. The interviews will be conducted using a qualitative research design with focus groups.

### 2.4. Participant timeline

Table 1 presents the schedule of enrollment, interventions, and assessments for this cRCT. Enrollment is scheduled between March and July 2024. Outcomes will be measured during the 2 weeks before and after the intervention.

**Table 1 TB1:** Schedule of enrollment, interventions, and assessments.

	**STUDY PERIOD**						
	**Enrollment**	**Allocation**	**Post-allocation**				
**TIMEPOINT**	**March-July 2024**	**Immediately after enrollment**	**Baseline**		**3-month follow-up**		**6-month follow-up (only CG)**
**ENROLLMENT:**							
**Eligibility screen**	X						
**Informed consent**	X						
**Allocation**		X					
**INTERVENTIONS:**							
**Intervention group (IG)**				[figure not shown]			
**Control group (CG)**						[figure not shown]	
**ASSESSMENTS:**							
**PA (step count; light, moderate, vigorous, and moderate-to-vigorous PA; sedentary time; and prolonged sedentary time)**			X		X		X
**Intensity of LBP**			X		X		X
**Disability due to LBP**			X		X		X
**Attitude/belief about LBP**			X		X		X
**Work productivity and activity impairment**			X		X		X
**Subjective improvement of LBP (PGIC)**					X		X
**Frequency of exercise**			X		X		X
**Work environment (temperature, relative humidity, lighting, and noise level)**			X		X		X
**Satisfaction with work environments (SAP)**			X		X		X
**Action to improve the telecommuting environment**			X		X		X
**Somatic symptoms (SSS-8)**			X		X		X
**Presenteeism (WHO-HPQ)**			X		X		X
**Work engagement (UWES-9)**			X		X		X
**Psychological outcomes (K6)**			X		X		X
**Participation and satisfaction**					X (only IG)		X
**Feasibility of and barriers to the program (interview)**					X (only IG)		

Abbreviations: CG, control group; IG, intervention group; K6, Kessler Psychological Distress Scale; LBP, low back pain; PA, physical activity; PGIC, Patient’s Global Impression of Change; SAP, Subjective Assessment of workplace Productivity; SSS-8, Somatic Symptom Scale-8; UWES-9, Utrecht Work Engagement Scale; WHO-HPQ, World Health Organization Health and Work Performance Questionnaire.

### 2.5. Sample size

The effect size of the intervention program regarding the primary outcome, a change in step count over 12 weeks, was estimated with Cohen *d* = 0.33. This is based on a previous study,^14^ with an SD of 2400 and an estimated difference between groups of 800 in the expected increase in step count. An increase of 800 steps is also a clinically meaningful difference.^38^ The calculation was performed with a type 1 error rate of 0.05 and a statistical power of 0.80, and the required sample size was estimated at 146 in each group for a total of 292 participants. To consider the design effect as a cRCT, the average number of cluster sizes was assumed to be 20, the intraclass correlation coefficient was 0.02, and the number of participants was calculated to be 403. Additionally, we estimated that 80% of the participants would finish the intervention; therefore, a total of 500 participants would be recruited. To improve the participation rate, some of the workplace-based results will be fed back to the employee coordinator in charge of each cluster for their health promotion strategies after the study is completed.

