### 2.6. Assignment of interventions

Stratified block randomization will be employed, and stratification will be based on the number of participants (<20 vs ≥20). Each cluster will be assigned to the intervention or control group based on a computer-generated random number table, which will be created by a biostatistician at the University of Tsukuba ([name]). It will be maintained by a researcher not associated with the research team at the Physical Fitness Research Institute, Meiji Yasuda Life Foundation of Health and Welfare. The allocation will be performed through central registration and disclosed to the participants and researchers via email. Due to the nature of the intervention, blinding was considered difficult to implement.

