### 2.8. Statistical methods

Efficacy will be analyzed using an intent-to-treat approach, regardless of adherence. The characteristics of the clusters and participants will be compared by group allocation using means (SDs) or medians (interquartile ranges) for continuous variables, and counts and percentages for nominal variables. The primary outcome, which is the change in daily step count between baseline and the end of the intervention, will be analyzed using generalized estimating equations (GEEs) to adjust for clustering. The GEE method will employ an exchangeable correlation structure and an identity link with a normal distribution. The mean model will include the allocated group as a factor and baseline step count as a covariate. We will analyze secondary outcomes (PA measures, LBP scale, and work environment scale) using the same method. A sensitivity analysis will be conducted for the primary outcome based on the per protocol set. All statistical tests will be 2-sided with a 5% significance level.

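### The design effect rests on an average cluster size of 20, the floor of the permitted 20 to 100, so the 80% power holds only if clusters stay small and similar in size

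*Protocol article*

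**What the plan says.** Section 2.5 of the protocol article starts from an effect that "was estimated with Cohen *d* = 0.33", "with an SD of 2400 and an estimated difference between groups of 800", and a "type 1 error rate of 0.05 and a statistical power of 0.80". This gives 146 per group, 292 in all. For clustering it states that "the average number of cluster sizes was assumed to be 20, the intraclass correlation coefficient was 0.02", which takes the total to 403. Expecting 80% to finish, it sets recruitment at 500.

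Cluster size appears in three other places:
- Abstract, Methods: "Randomization will be conducted on a stratified block basis for clusters of 20 to 100 individuals within the recruited companies".
- Section 2.1, where clusters are formed from employees who have agreed to take part: "clusters of 20 to 100 participants will be selected and allocated to units".
- Section 2.6: "stratification will be based on the number of participants (<20 vs ≥20".

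Section 2.8 analyses the primary outcome by GEE with an exchangeable correlation and baseline steps as a covariate, and says: "All statistical tests will be 2-sided with a 5% significance level".

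**The concern.** The average used for the design effect equals the smallest cluster that the abstract and section 2.1 permit. A mean at the floor of a range running to 100 is possible only if hardly any of that range is used. The stratum for fewer than 20 in section 2.6 points the other way: it has no purpose if 20 is the minimum. If such clusters are admitted, a mean of 20 becomes possible alongside large clusters, but sizes would then be unequal, and the simple design effect makes no allowance for that.

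At stake is how the primary result is read. The article calls 800 steps clinically meaningful and claims 80% power to detect it. If clusters turn out larger or more uneven than assumed, a null result would be taken as stronger evidence against an 800-step effect than the trial can give.

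**Working it through.** **Inputs.** From section 2.5: d = 0.33 (800/2400 = 0.333), ICC = 0.02, average cluster size 20, retention 80%, 500 recruits. From section 2.8: two-sided 5% tests.

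**The plan's own figures.**
- For d = 0.33, power 0.80 and two-sided 0.05, the t-test solution is 145.1, so 146 per group and 292 in total.
- Design effect DE = 1 + (20 − 1) × 0.02 = 1.38, and 292 × 1.38 = 402.96, so 403.
- 403 / 0.8 = 503.75, against a stated 500. The rounding is immaterial.

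The chain reproduces.

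**Recruited or analysed size.** Section 2.1 counts consenting employees, so 20 to 100 is recruited size. Section 2.5 applies 1.38 to the number analysed and inflates for dropout afterwards. With M the recruited mean, the analysed mean is m = 0.8M. An analysed mean of 20 therefore means 20 / 0.8 = 25 recruited.

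**Power of 500 recruits.** There are 500 × 0.8 = 400 completers. For equal clusters, DE = 1 + (m − 1) × 0.02, effective N = 400/DE, and power is approximately Φ(0.33 × √(effective N / 4) − 1.96). Recruits needed for 80% are 292 × DE / 0.8.

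| Recruited mean M | Analysed m | DE | Effective N | Power | Recruits needed |
|---|---|---|---|---|---|
| 20 | 16 | 1.30 | 307.7 | 82.5% | 475 |
| 25 | 20 | 1.38 | 289.9 | 80.2% | 504 |
| 30 | 24 | 1.46 | 274.0 | 78% | 533 |
| 40 | 32 | 1.62 | 246.9 | 74% | 592 |
| 60 | 48 | 1.94 | 206.2 | 66% | 709 |

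The means of 30, 40 and 60 are assumptions, because the article gives none.

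**Break-even.** With d = 0.33, 80% power needs an effective N of 4 × (1.96 + 0.8416)² / 0.33² = 288.3. That gives DE = 400 / 288.3 = 1.387, so m = 1 + 0.387/0.02 = 20.4, or about 25 recruited. With 800/2400 in place of 0.33, m is 21.8, or about 27 recruited.

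**Detectable difference.** With SD 2400, the difference detectable at 80% is 2.8016 × 2400 × √(4 × DE / 400) = 672.4 × √DE. For recruited means of 30, 40 and 60 this is about 812, 856 and 937 steps.

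**Unequal sizes.** DE = 1 + [(1 + CV²)m − 1] × 0.02. Take a recruited mean of 20 (m = 16), with the CV assumed:
- CV 0.6: DE = 1 + (1.36 × 16 − 1) × 0.02 = 1.415, power about 79%.
- CV 1.0: DE = 1 + (2 × 16 − 1) × 0.02 = 1.62, power about 74%.

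**Two layouts within the permitted 20 to 100, each totalling 500 recruits.**
- One cluster of 60 and twenty-two of 20: analysed sizes 48 and 16, DE = 1 + [(48² + 22 × 16²)/400 − 1] × 0.02 = 1.377, power about 80%.
- One cluster of 100 and twenty of 20: analysed sizes 80 and 16, DE = 1 + [(80² + 20 × 16²)/400 − 1] × 0.02 = 1.556, power about 75%. Exchangeable GEE weights large clusters down. On that basis effective N is 80/2.58 + 20 × 16/1.30 = 277.2, and power is about 78%.

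**The case against.** A reader might infer that the design effect is too small however the text is read, and that 80% power is simply unavailable. The documents do not support that. Since 20 to 100 is recruited size, an analysed mean of 20 corresponds to 25 recruited, which is above the floor and need not mean identical clusters. Layouts that obey the stated rules reach 80%, as the working shows. Nor is this an arithmetic error, since every step of the calculation reproduces.

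Treating 30, 40 and 60 as analysed sizes would give 75%, 70% and 61%, but that overstates the loss because it ignores the expected dropout. The midpoint of 60 is not a forecast, and the CVs are illustrative.

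It is also tempting to add a t reference on clusters minus 2 degrees of freedom, which lowers power further. The article specifies no such reference, and small-sample corrections are commonly left to the analysis plan. It would take even 25 equal clusters of 20 recruits to just under 80%, so it does not measure the cluster-size problem.

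The best counter-argument is baseline adjustment. Section 2.8 includes baseline steps, and section 2.5 takes no credit for them. If 2400 is the SD of change, variances are equal at both times and the ICC is unchanged, adjustment multiplies the variance by (1 + r)/2. For an assumed r of 0.5 to 0.8, power at a recruited mean of 40 becomes about 85% to 78%. That could offset much or all of the loss, but no correlation is given, so it cannot be relied on.

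What remains is that the cluster-size figures disagree and the power claim carries no condition.

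**Conclusion.** The point stands in conditional form. Section 2.5 takes its average from the floor of the range in the abstract and section 2.1, allows nothing for unequal sizes, and sits beside a stratum in section 2.6 that contradicts that floor. Power is about 80% while the recruited mean is no more than about 25 to 27 with little variation. Above that it falls, to 66% at a recruited mean of 60. These figures assume 400 completers, the plan's d and ICC, a normal approximation and no credit for baseline adjustment. The size of any shortfall is unknown because the article states neither the expected mean nor the spread. The point concerns power only; it shows no bias and no inflation of the type 1 error.

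**What to change.** In section 2.5, replace the unqualified 80% with the power, or the detectable difference, that 500 recruits give under the cluster sizes actually expected or enrolled. State the mean and CV used, with DE = 1 + [(1 + CV²)m − 1] × ICC and m as the analysed size. If credit is taken for baseline adjustment, state the assumed correlation.

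Make the size range and the stratum boundary agree across the abstract and sections 2.1, 2.5 and 2.6: either 20 is a minimum and the lower stratum goes, or smaller clusters are allowed and the range says so.

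This needs no extra participants. The cost is some rewording and possibly a less favourable power figure.
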